## Abstract

**Background:**

While high-quality meta-analyses have confirmed the effectiveness of aphasia therapy after stroke, there is limited evidence for the comparative effectiveness of different aphasia interventions. Two commonly used interventions, Constraint-induced Aphasia Therapy Plus (CIAT Plus) and Multi-modality Aphasia Therapy (M-MAT), are hypothesised to rely on diverse underlying neural mechanisms for recovery and may be differentially responsive to aphasia severity. COMPARE is a prospective randomised open-blinded end-point trial designed to determine whether, in people with chronic post-stroke aphasia living in the community, CIAT Plus and M-MAT provide greater therapeutic benefit compared to usual care, are differentially effective according to aphasia severity, and are cost-effective. This paper details the statistical analysis plan for the COMPARE trial developed prior to data analysis.

**Methods:**

Participants (*n* = 216) are randomised to one of three arms, CIAT Plus, M-MAT or usual care, and undertake therapy with a study trained speech pathologist in groups of three participants stratified by aphasia severity. Therapy occurs for 3 h blocks per day for 10 days across 2 weeks. The primary clinical outcome is aphasia severity as measured by the Western Aphasia Battery-Revised Aphasia Quotient (WAB-R-AQ) immediately post intervention. Secondary outcomes include WAB-R-AQ at 12-week follow-up, and functional communication, discourse efficiency, multimodal communication, and health-related quality of life immediately post intervention and at 12-week follow-up.

**Results:**

Linear mixed models (LMMs) will be used to analyse differences between M-MAT and UC, and CIAT-Plus and UC on each outcome measure immediately and at 12 weeks post-intervention. The LMM for WAB-R-AQ will assess the differences in efficacy between M-MAT and CIAT-Plus. All analyses will control for baseline aphasia severity (fixed effect) and for the clustering effect of treatment groups (random effect).

**Discussion:**

This trial will provide relative effectiveness data for two common interventions for people with chronic post-stroke aphasia, and highlight possible differential effects based on aphasia severity. Together with the health economic analysis data, the results will enable more informed personalised prescription for aphasia therapy after stroke.

**Trial registration:**

Australian New Zealand Clinical Trials Registry: ACTRN 12615000618550. Registered on 15 June 2016

## Introduction

Aphasia is an acquired language disability, impacting all aspects of communication underpinned by language: speech, reading, writing, and speaking. Aphasia is present in approximately one third of stroke survivors [1], with significant negative impacts on mental health [2] and quality of life [3]. The 2016 Cochrane review of speech and language therapy for aphasia after stroke analysed 57 aphasia therapy trials and showed statistically significant treatment effects immediately after intervention but not at follow-up [4]. Although there is a broad range of approaches to aphasia intervention there is extremely limited evidence concerning their differential effects [4]. Two commonly utilised therapies, Constraint-induced Aphasia Therapy Plus (CIAT Plus) [5] and Multi-modality Aphasia Therapy (M-MAT) [6] are both intensive, high-dose interventions aimed at improving verbal communication. However, they are hypothesised to rely on different underlying neural recovery mechanisms and importantly may be differentially effective based on overall aphasia severity. Determining the most effective intervention for sub-groups of patients with aphasia may lead to improved patient outcomes and reduced health care costs.

COMPARE is a prospective, assessor-blinded, randomised clinical trial with a group- randomised design, operating in community sites across Australia and New Zealand. The primary aim of the COMPARE trial is to determine whether two contrasting, intensive treatments for chronic post-stroke aphasia, CIAT Plus and M-MAT, are superior to non-standardised, limited aphasia therapy in the community (usual care: UC). The primary endpoint is improvement on the WAB-R-AQ [7] at therapy completion. A range of other aims are addressed through secondary hypotheses listed below. Ethics and local governance approval were obtained from all hospital and university sites supporting recruitment. Version 5.2 of the protocol, dated 7 May 2019, is current and the study protocol has been published [8].

### Primary hypothesis

Compared to UC, both CIAT Plus and M-MAT will result in reduced aphasia severity as measured by the WAB-R-AQ immediately post intervention.

### Secondary hypotheses

Compared to UC, CIAT Plus and M-MAT will result in:
Reduced aphasia severity on the WAB-R-AQ [7] at 12-week follow-up.Significantly more efficient connected speech (Content Information Units [CIUs] per minute [9]) immediately post intervention and at 12-week follow-up.Significantly better ratings of functional communication (Communicative Effectiveness Index [CETI] [10]) immediately post intervention and at 12-week follow-up.Significantly better multimodal communication (Scenario Test [11]) immediately post intervention and at 12-week follow-up.Significantly better quality of life (Stroke and Aphasia Quality of Life Scale-39 g [SAQOL-39 g] [12]) immediately post intervention and at 12-week follow-up;and we will also determine whether:
6.M-MAT will be more effective in reducing aphasia severity (WAB-R-AQ [7]) immediately post intervention and at the 12-week follow-up than CIAT Plus for mild and severe aphasia, whereas CIAT Plus will be more effective than M-MAT for moderate aphasia, and7.The interventions when compared to UC are cost-effective.

The trial protocol includes additional hypotheses related to a number of tertiary outcomes including an optional sub-study. The economic evaluation for the main trial and the analysis of the tertiary outcomes will be published separately. This paper provides a detailed description of the COMPARE statistical analysis plan (SAP Version 1.1 dated September 18, 2020) and has been prepared in accordance with the published guidelines on the context of statistical analysis plans [13].

## Summary of the study protocol

Written, informed consent is obtained from each participant and their carer/significant other using hospital- and university-approved consent processes supported by aphasia friendly consent documents. Participants enrolled in the trial are allocated to treatment groups of three participants, based on their aphasia severity (as determined by the Western Aphasia Battery-Revised-Aphasia Quotient [WAB-R-AQ] [2]) and geographic location.

### Patient population

Participants include adults (18 years of age or older) living in the community who were diagnosed with any type of aphasia (WAB-R-AQ < 93.8) following a stroke at least 6 months prior to enrolment in the trial. Participants are recruited through 22 hospitals with ethical approval for the study and direct community advertising in Australia and New Zealand. Inclusion criteria and exclusion criteria are listed in the main protocol [8].

### Randomisation

Eligible participants are randomised to one of three arms: CIAT Plus, M-MAT, or UC. The intervention protocol requires therapy to be provided face-to-face, in groups of three participants. The members of a treatment group therefore need to be in the same geographic location. The trial uses a stratified group-randomisation strategy. Once enrolled in the trial, participants are allocated to treatment groups based on their aphasia severity (WAB-R-AQ mild = 93.7–62.6; moderate = 62.5–31.3; severe < 31.3). The groups are then randomised to one of three arms (M-MAT, CIAT Plus or UC) in a 1:1:1 ratio via a central allocation system using blocked randomisation within each stratum.

### Intervention

Participants randomised to the CIAT Plus and M-MAT arms of the trial attend treatment sessions 3 h a day, five times a week for 2 weeks (30 h of treatment in total). In addition, a daily home practice communication task (15 min) is given to each participant and checked for completion and logged the following day. CIAT Plus and M-MAT are provided in community settings by a qualified and study-trained speech pathologists. The UC arm is the control arm of the trial. Participants randomised to the UC arm undergo aphasia therapy in the community at the type and frequency that is available to them at the time of their recruitment and randomisation. For some participants, UC may comprise no direct intervention, while for others it may take the form of non-intense, individual, computerised or social/support group sessions (expected to be < 2 h per week). Full details of the intervention are provided in the COMPARE Trial protocol [8].

### Sample size considerations

The study is powered to detect a difference of 5 points on the WAB-R-AQ [7] at therapy completion. Although the minimal clinically important difference for the WAB-R-AQ [7] has not been formally determined, the standard error of measurement for participants with chronic aphasia is 4.33 points [21] with a 5-point difference considered clinically meaningful [22]. We used this information to estimate the required sample size in two steps. First, we conducted a naïve power analysis (which did not account for the clustering effect of conducting therapy in groups) which indicated a sample size of 198 to achieve 80% power at the 5% significance level. In the second step, we adjusted for the clustering effect of group therapy since the outcomes of participants from within the treatment cluster may be correlated. We anticipated a relatively small intraclass correlation coefficient (ICC) of 0.04. This is consistent with estimates of ICC used in other studies, where prior information on the size of the intraclass correlation was not available. Based on this intraclass correlation coefficient and a group size of 3, we calculated a maximum design effect of 1.08. To adjust for the clustering effect, we multiplied this value by the design effect, and rounded off to a multiple of 3, to obtain balanced allocation across the three treatment groups. This yielded the required sample size of 216.

### Other data collection

Other data collected, including tertiary outcomes, resource use (for the economic evaluation) and therapy characteristics are described in the main trial protocol [8]. Collection of data related to therapy characteristics and adverse events is summarised below.

During the trial intervention period, a daily log is completed for each trial participant which includes content, duration and frequency of sessions, nature of home tasks prescribed and completed, and participant self-rated fatigue and distress. All trial data is logged in individual electronic case report forms in a customised REDcap database. Deviation from the prescribed therapy protocol (CIAT Plus and M-MAT) is documented. Reasons for withdrawal from the trial such as health-related complications and death are recorded. A participant diary is provided to capture information on usual care therapy. Participants are questioned about general health to determine if there have been any adverse or serious adverse events during the trial period.

### Blinding

COMPARE is a complex behavioural intervention in which the treating therapists are aware of the treatment that they are providing. Participants assigned to UC will be aware that they are not receiving intense treatment. Therefore, neither the participants nor the treating therapists are considered to be blinded. However, all assessments (baseline, immediate post intervention, follow-up) are conducted by independent assessors who are blinded to treatment allocation.

### Unblinding

Only the Data and Safety Monitoring Committee (DSMC) have access to progressive data. The DSMC Chair is [name], University of Melbourne, Victoria, Australia. The DSMC review unblinded data in accordance with the DSMC Charter (Version 1.0, 10 November 2016).

## Statistical analysis plan

### Analysis principles and general considerations

All outcomes and analyses are prospectively characterised as primary or secondary. Differences in all endpoints between the three arms of the trial (CIAT Plus, M-MAT, UC) will be tested independently at the two-tailed 5% significance level. All estimates of treatment effects will be presented with 95% confidence intervals. No formal adjustments will be undertaken to constrain the Type I error associated with planned secondary or exploratory analyses. The information provided by analyses is designed to supplement the evidence from the primary analyses; it will provide a more complete characterisation of the treatment effects.

### Intention to treat, sensitivity and per-protocol analyses

The analyses for all outcome measures (aphasia severity, communication efficiency, functional communication, total communication, quality of life) will be conducted on an intention the treat (ITT) basis, that is, all participants will be analysed as members of the group to which they were randomised, irrespective of whether they received the allocated treatment or not. The ITT strategy for COMPARE is based on the following principles:
All available outcome data are collected on all randomised participantsAll participants are analysed in the groups to which they are randomised.All available outcome data will be used in the primary analyses. The primary analyses will be reported without imputation of missing data. If the amount of missing data exceeds 10% at the primary endpoint (therapy completion), missing data will be imputed under the assumption that data is missing at random.A sensitivity analysis including all randomised individuals will be conducted. The sensitivity analysis will consider alternative assumptions about data missing not at random (MNAR).

Given COVID-19 pandemic impacts on face to face assessments from March 23, 2020, some trial assessments may be undertaken via videoconferencing. Assessments undertaken via videoconferencing are considered to be reliable and are expected to be consistent with face-to-face assessments [23]. These will therefore be included in the ITT analysis. The assessments conducted via videoconferencing will be assessed for consistency with the face-to-face assessments by comparing each online assessment to:
The mean for participants with similar baseline characteristics, who received face-to-face assessments at the given timepoint.The mean change from previous timepoint for participants with similar baseline characteristics, who received face-to-face assessments at the given timepoint.A sensitivity analysis will be performed if the assessments conducted via videoconferencing (or change from previous timepoints) are found to be more than 3 standard deviations from the relevant mean face-to-face assessment (or relevant mean change).

A per-protocol analysis may be conducted separately but will not be included in the primary results publication for this trial. The per-protocol analysis will be described in a separate publication and will be based on the following principles:
The per-protocol cohorts will be based on whether or not participants received the planned minimum 27 h/27 sessions of aphasia therapy completed in the CIAT Plus/M-MAT therapy groups.Participants from the CIAT Plus/M-MAT groups who do not achieve the minimum therapy amount specified in the protocol will be treated as not compliant with the treatment protocol and will be included in the control group.All participants who are randomised to the UC group will be included in the control group.

For primary and secondary analyses, the treatment effects for the primary effectiveness outcomes will be adjusted for baseline aphasia severity, measured by the WAB-R-AQ [7] and baseline stroke severity measured by the mRS [15]. Unadjusted analyses will be reported separately from these pre-specified analyses.

Subgroup analyses will be carried out irrespective of whether there is a significant treatment effect on the primary outcome. Their purpose is to supplement evidence from the primary analyses to help to fully characterise the treatment effect. Results from subgroup analyses will be interpreted in this context.

All analyses will be conducted using the R Statistical Programming Language [24].

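### The 3 SD trigger for videoconference assessments screens single scores for outliers and is a poor detector of a systematic shift between assessment modes; the analysis without online assessments should always be run.

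*SAP article*

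**What the plan says.** The COVID-19 paragraph of the SAP article (section on intention to treat, sensitivity and per-protocol analyses) allows remote assessment from 23 March 2020. It states: "Assessments undertaken via videoconferencing are considered to be reliable and are expected to be consistent with face-to-face assessments". On that basis it keeps all online assessments in the intention-to-treat analysis.

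Consistency is checked one assessment at a time. Each online result is set against two references from face-to-face participants with similar baseline characteristics: their mean at that timepoint, and their mean change since the previous timepoint. A sensitivity analysis follows only if online assessments "are found to be more than 3 standard deviations from the relevant mean face-to-face assessment", or equally far from the mean change.

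Nothing else in the article deals with assessment mode. The sections on treatment of missing values and on sensitivity analyses concern missing data only.

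**The concern.** If video assessment alters scores, the likely form is a modest shift in the average. A 3 SD limit on individual results is built to catch single wild values. A shift the size of the trial's own target difference could leave nearly every score inside the limit, so no sensitivity analysis would be run. Silence from the check could then be taken as support for the expected consistency, although the check had little chance of contradicting it.

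At stake are the contrasts that include online data: WAB-R-AQ after therapy and at 12 weeks, and the secondary outcomes. They are affected to the extent that the share of online assessments differs between arms.

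**Working it through.** **The plan's own figure.** "The study is powered to detect a difference of 5 points on the WAB-R-AQ", with a "sample size of 198 to achieve 80% power at the 5% significance level". Allocation is "in a 1:1:1 ratio via a central allocation system", so 198/3 = 66 per arm. Endpoints are "tested independently at the two-tailed 5% significance level". With an "intraclass correlation coefficient (ICC) of 0.04" and "a group size of 3, we calculated a maximum design effect of 1.08": 1 + (3 − 1) × 0.04 = 1.08, and 198 × 1.08 = 213.84. The next multiple of 3 is 216. The stated sample size reproduces.

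**SD (assumption).** No SD is given. Inverting the 198:

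SD = 5 / [(1.96 + 0.84) × √(2/66)] = 10.25

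Other readings of the calculation give 9.2 to 11.6. For change scores, the stated standard error of measurement of 4.33 gives a floor of 4.33 × √2 = 6.12, which assumes independent errors and no true variation in change.

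**Size of the limit.** 3 × 10.25 = 30.8 points for scores. This is about six times the 5-point target and close to one severity band (62.5 − 31.3 = 31.2). For change at the floor it is 3 × 6.12 = 18.4 points.

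**Chance that one score is flagged under a uniform shift of 5 points** (normal scores): P = 1 − Φ(3 − 5/SD) + Φ(−3 − 5/SD).

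- SD 10.25: 5/10.25 = 0.49, P = 0.62%
- SD 6.12: 5/6.12 = 0.82, P = 1.46%
- No shift: P = 0.27%

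**Chance of at least one flag among m independent online scores**, 1 − (1 − P)^m. The number m is not stated; 10 to 40 is assumed, and one flag is taken as enough to trigger the analysis.

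| | m = 10 | m = 20 | m = 40 |
|---|---|---|---|
| Scores, SD 10.25, 5-point shift | 6% | 12% | 22% |
| Change, SD 6.12, 5-point shift | 14% | 25% | 44% |
| Either comparison alone, no shift | 3% | 5% | 10% |

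Adding the two flag rates (0.62% + 1.46%, about 2.1% per score) and ignoring overlap, which favours the plan: 1 − 0.979^20 = 35% and 1 − 0.979^40 = 57%.

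**Range.** With SD 15 to 20 for scores, 20 online scores give 7% to 8%. At the extreme where matched participants differ only by measurement error (SD 4.33), the limit is 13.0 points and 20 scores give 48%. If the rule is instead read as the online mean lying 3 SD away, a 5-point shift triggers it with probability below 0.00002 once there are 5 or more scores.

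**Effect on a treatment contrast.** Bias = mode shift × between-arm difference in online share. With 216/3 = 72 per arm and a 5-point shift, purely as illustration:

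- 12 online in one arm and 6 in another: 5 × 6/72 = 0.4 points
- 18 and 0: 5 × 18/72 = 1.25 points

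**Timing.** The last follow-up was on 23 July 2020 (Summary section). Twelve weeks earlier is 30 April 2020. At nominal visit timing, online primary-endpoint assessments fall between about 23 March and 30 April, and later ones are 12-week follow-ups.

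**What a direct comparison of means could do.** Take about 216 × 0.94 = 203 observed scores (the article reports 6% missing at the primary endpoint) and SE = SD × √(1/m + 1/(203 − m)).

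- m = 20: 95% CI half-width 4.7 points at SD 10.25 and 2.8 at SD 6.12; power for a 5-point shift at two-sided 5% is 54% and 93%
- m = 40: half-width 3.5 and 2.1; power 79% and above 99%

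**The case against.** The strongest reply has four parts.

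- **The check has two limbs, and the change limb is the sharper one.** This stands. At the floor SD it gives 25% against 5% with no shift at 20 scores, so it does separate the two to some degree. With both limbs and 40 scores, a flag becomes more likely than not. It would therefore go too far to say that a 5-point shift always passes unnoticed.
- **Harm to the primary result is small.** This stands too. A reader might infer that a 5-point mode shift biases the treatment effect by 5 points. That would need one arm entirely online and the other entirely face-to-face. The window for online primary assessments is short, and blocked randomisation within severity strata makes gross imbalance less likely.
- **A mode shift is hypothetical.** Nothing in the article suggests one, and the reliability claim cites a source not available here. But the check exists to test that expectation, so the expectation cannot excuse a check with little power to contradict it.
- **A mode coefficient is no cure.** Online assessment occurs only in the pandemic period, so mode and period are confounded, and with few online scores the estimate is imprecise. This stands, and is why the exclusion analysis should lead.

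Three further inferences lack support. The article does not say that it will report the modes as consistent. It does not say that whole therapy groups were assessed online. Nor is the limit generally out of reach: with an invented mean of 75 and SD of 10, the upper limit of 105 exceeds the scale maximum of 100, but the lower limit of 45 can be reached.

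**Conclusion.** The concern holds as a weakness of the trigger. On the assumed 10 to 40 online scores, a systematic 5-point shift prompts the sensitivity analysis in 6% to 22% of cases on scores and 14% to 44% on change. With both limbs added, the figures are about 35% at 20 scores and 57% at 40. Even when a flag occurs, it marks a chance outlier and does not estimate the shift.

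These percentages depend on an SD and a count that the article does not give, on normality and on independent scores. That a limit on single scores is ill suited to finding a shift in the mean does not depend on them.

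The documents do not support a claim that the primary result is materially biased. The likely effect there is small, and the point matters more for the 12-week outcomes. The sample size of 216 is not in question. This is a cheap improvement worth making.

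**What to change.** Drop the 3 SD trigger. For every outcome and timepoint with online assessments:

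1. Always repeat the main model without the online assessments, and report the number of online assessments by arm.
2. As a supporting analysis, add an assessment-mode indicator to the main model: a simple fixed effect in the single-timepoint primary model, and a time-varying one in the longitudinal models. Report its estimate with a 95% confidence interval. State that mode is confounded with the pandemic period and that the estimate will be imprecise if few assessments were online.

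The cost is two extra model runs per analysis and slightly lower precision in the exclusion analysis. No new outcome data are needed.

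### The optional per-protocol analysis counts under-treated CIAT Plus and M-MAT participants as controls, which makes it an as-treated comparison that can be biased in either direction

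*SAP article*

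**What the plan says.** The rule is in the SAP article, section Intention to treat, sensitivity and per-protocol analyses. Compliance depends on whether a participant "received the planned minimum 27 h/27 sessions of aphasia therapy completed in the CIAT Plus/M-MAT therapy groups". Active-arm participants who fall short "will be treated as not compliant with the treatment protocol and will be included in the control group". The section adds: "All participants who are randomised to the UC group will be included in the control group".

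The same section limits the role of this analysis: "A per-protocol analysis may be conducted separately but will not be included in the primary results publication for this trial". All outcome measures are to be analysed by intention to treat (ITT).

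The Intervention section sets the active schedule at 3 h a day, "five times a week for 2 weeks", 30 h in total. UC is expected to be under 2 h a week, and "For some participants, UC may comprise no direct intervention".

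**The concern.** A per-protocol analysis normally leaves deviators out. This one relabels them as controls, which breaks randomisation on both sides of the contrast:

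- The active arms keep only participants who completed enough therapy. If completion tracks prognosis, those arms are selected.
- The control group gains the participants removed from both active arms. They may have a different prognosis, and they may have had up to just under 27 h of trial therapy, while UC is expected to supply under 2 h a week.
- Therapy groups of three are the unit of randomisation and the random effect in the models. Moving individuals can put members of one group in different analysis arms, and the article does not say how the random effect would then be handled.

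The adjustment named for the primary and secondary analyses (baseline WAB-R-AQ and mRS), if carried over, does not remove selection on unmeasured factors. A separate paper presenting the result as per-protocol evidence could therefore report a benefit that does not exist, or understate one that does.

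**Working it through.** **The plan's own figure.** Design effect = 1 + (3 − 1) × 0.04 = 1.08. 198 × 1.08 = 213.84, and the next multiple of 3 is 216, as stated. With 1:1:1 allocation that is 72 per arm, so 144 active and 72 UC. The point does not depend on this figure beyond the arm sizes.

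**Inputs.** From the SAP article: 72 per arm and a 5-point target difference. Assumed, because the documents give no values:

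- p, the non-compliance share in each active arm;
- d, the prognostic difference of non-compliers against compliers that remains after covariate adjustment (negative = worse);
- f, the share of the full effect D that non-compliers obtain from partial therapy.

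**Formula.** Set the untreated mean of each randomised arm to 0. Compliers then have untreated mean −p·d and non-compliers (1 − p)·d. The control group has 72 UC plus 144p non-compliers. The expected contrast of one active arm with the pooled controls is

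D − p·d − 2p[(1 − p)d + f·D] / (1 + 2p).

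Excluding non-compliers and keeping UC as randomised gives D − p·d.

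**No true effect (D = 0), d = −5**

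| p | From selecting compliers | From lowering the control mean | Planned rule | Exclusion |
|---|---|---|---|---|
| 10% | 0.50 | 0.75 | 1.25 | 0.50 |
| 15% | 0.75 | 0.98 | 1.73 | 0.75 |
| 30% | 1.50 | 1.31 | 2.81 | 1.50 |

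At 15%, for example, the control mean is 21.6 × (−4.25) / 93.6 = −0.98. Here the bias is proportional to d: a 2.5-point gap halves it, to about 0.63 at 10% and 1.41 at 30%.

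**True effect 5, no prognostic gap, non-compliers gaining 4 (f = 0.8)**

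- 15%: control mean 21.6 × 4 / 93.6 = 0.92; contrast 5 − 0.92 = 4.08.
- 30%: control mean 43.2 × 4 / 115.2 = 1.50; contrast 5 − 1.50 = 3.50.

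**Both mechanisms together, D = 5, p = 20%**

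| d | f | Planned rule | Exclusion |
|---|---|---|---|
| −5 | 0 | 7.14 | 6.00 |
| −5 | 0.9 | 5.86 | 6.00 |
| 0 | 0 | 5.00 | 5.00 |
| 0 | 0.5 | 4.29 | 5.00 |
| +5 | 0.5 | 2.14 | 4.00 |

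The sign of the bias depends on unknown quantities. It is zero only in special cases, such as non-compliers with the same prognosis as compliers and no benefit from partial therapy.

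**Type I error.** The article states no SD. Inverting the two-means formula for 66 per arm (198/3), a 5-point difference, 80% power and two-sided 5% implies an SD of 10.25. In 20,000 simulated null trials with that SD, a t test and no clustering, a gap of 5 points in either direction gave a rejection rate of about 11% at 10% non-compliance and about 23% at 20%, against about 5% for ITT.

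**Check on the alternative.** A complier-average causal effect (CACE) divides the ITT effect by the share reaching the threshold. Under the null it is centred on 0. With D = 5 and non-compliers gaining 4:

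- 15%: ITT = 0.85 × 5 + 0.15 × 4 = 4.85; CACE = 4.85 / 0.85 = 5.71.
- 30%: ITT = 0.70 × 5 + 0.30 × 4 = 4.70; CACE = 4.70 / 0.70 = 6.71.

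So a binary threshold overstates the effect if partial therapy helps. This must be disclosed.

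**Threshold against schedule.** The schedule gives 10 daily attendances and 30 h. A minimum of 27 hours, or 27 sessions, fits it if a session lasts one hour. It does not fit if a session is a day's block. The article does not define the term.

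**The case against.** Four objections carry weight.

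- **Reach.** The analysis is optional and kept out of the primary results publication. A reader might infer that the trial's main conclusions are compromised. The documents do not support that: the primary and secondary analyses are ITT, and neither they nor the sample size use this rule. This stands and limits the severity.
- **The session count.** A reader might infer that nobody can reach 27 sessions in 10 days, so that every active participant would become a control. That requires a session to mean a whole day and the slash to mean that both conditions must be met. Pairing 27 h with 27 sessions reads more naturally as hourly sessions, 27 of 30. What remains is an undefined term.
- **Size.** No document gives a non-compliance rate, a prognostic gap or the benefit of partial therapy. A 5-point gap after adjustment is large, about half the implied SD. The article lists health-related complications as reasons for withdrawing from the trial, not for missing therapy hours, and participants who withdrew may have no post-intervention outcome. The figures therefore show a mechanism and do not estimate this trial's bias.
- **The alternatives are imperfect.** With partial benefit, the CACE is off by +0.71 at 15% and +1.71 at 30%, against −0.92 and −1.50 for the planned rule. Exclusion is also non-randomised, and it is slightly worse than the planned rule in one scenario above (6.00 against 5.86).

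None of this defends the reallocation itself. The CACE keeps the randomised arms and is centred on zero when there is no effect. The planned rule is not, once prognosis differs.

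**Conclusion.** The rule is wrong as written: it is an as-treated comparison labelled per-protocol, with a bias of unknown direction. Under the stated assumptions, a null effect appears as a benefit of about 1.3 to 2.8 points at 10% to 30% non-compliance, compared with the 5-point target. A true effect of 5 with substantial partial benefit appears as about 4.1 (15%) to 3.5 (30%). These values rest on an assumed 5-point residual gap in the first case, and in the second on an assumed 4-point gain with no gap. The point should be fixed before any per-protocol paper is prepared; it is not a defect of the primary analysis. The session wording is a minor matter, relevant because the threshold decides who is classed as non-compliant.

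**What to change.** 1. Delete the sentence that places non-compliers in the control group, and keep UC as randomised.
2. Estimate the effect of receiving therapy for each active arm against UC, with randomised arm as the instrument for reaching the minimum. Adjust for baseline WAB-R-AQ and mRS, and cluster by therapy group. State that a binary threshold overstates the effect if therapy below it helps.
3. Add a sensitivity analysis with logged therapy hours as the treatment received. The daily logs described under Other data collection already record session duration and frequency.
4. If a conventional per-protocol set is also shown, exclude non-compliers and label the comparison non-randomised.
5. Reconcile the 27-hour, 27-session threshold with the schedule in the Intervention section by stating what a session is.

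The cost is SAP wording and a few lines of code, with no new data. The price in inference is a wider confidence interval than the as-treated comparison and reliance on the stated instrument assumptions.
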